## Abstract

**Background:**

Sedentary behavior (SB) has been linked to several negative health outcomes. Therefore, reducing SB or breaking up prolonged periods of SB improves functional fitness, food consumption, job satisfaction, and productivity. Reducing SB can be achieved by introducing a health-enhancing contextual modification promoted by a sit-stand desk in the workplace. The primary goal will be to test the effectiveness of this intervention in reducing and breaking up SB, while improving health outcomes in office-based workers during a 6-month intervention.

**Methods:**

A two-arm (1:1), superiority parallel-group cluster RCT will be conducted to evaluate the effectiveness of this intervention in a sample of office-based workers from a university in Portugal. The intervention will consist of a psychoeducation session, motivational prompts, and contextual modification promoted by a sit-stand desk in the workplace for 6 months. The control group will work as usual in their workplace, with no contextual change or prompts during the 6-month intervention. Three assessment points will be conducted in both groups, pre-intervention (baseline), post-intervention, and a 3-month follow-up. The primary outcomes include sedentary and physical activity-related variables, which will be objectively assessed with 24 h monitoring using the ActivPAL for 7 days. The secondary outcomes include (a) biometric indices as body composition, body mass index, waist circumference, and postural inequalities; and (b) psychosocial variables such as overall and work-related fatigue, overall discomfort, life/work satisfaction, quality of life, and eating behavior. Both the primary and secondary outcomes will be assessed at each assessment point.

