### Objectives {7}

This paper describes the protocol for a cluster randomized controlled trial (RCT) the Standing Up for Healthy Aging (SUFHA), which aims to evaluate the change in sedentary patterns (i.e., quantity and accumulation pattern) resulting from the introduction of a health-enhancing contextual modification (i.e., sit-stand desk) in the workplace, compared to a control group after 6 months of intervention (i.e., effectiveness). Secondary outcomes are body composition, eating patterns, health and work-related outcomes, skeletal muscle discomfort, well-being, and quality of life. Additionally, we aim to crossover the intervention and test the impact of 3 months without the sit-stand desks on sedentary patterns in the intervention group and the impact of 3 months of sit-stand desks in the control group, and the level of acceptance regarding the use of these sit-stand desks in both groups.

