### Outcomes {12}

#### Primary

The primary outcomes of SUFHA are the sedentary and PA-related outcomes (e.g., minutes of SB/day, minutes of sitting time/day, minutes of standing time/day, sit-to-upright transitions/day, number of steps, among others), which will be objectively assessed with 24-h monitoring using the ActivPAL for 7 consecutive days. Changes in these parameters are the main goal of the current RCT (i.e., effectiveness). More details regarding the assessment that generate these outcomes can be found in the “Data collection and management” section. These outcomes will be measured at baseline (i.e., a week within the 30 days prior to the installation of the sit-stand desks), 2nd moment (i.e., final month of intervention), and 3rd moment (i.e., final month of follow-up). Additionally, in the third month of intervention, all participants will be challenged to use the ActivPAL. Although this assessment moment is not mandatory, we expect a significant adherence to this challenge.

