## Data collection and management

### Plans for assessment and collection of outcomes {18a}

#### Primary data collection

##### Sedentary and PA pattern assessment

We will collect sedentary and PA pattern data derived from an ActivPAL inclinometer/accelerometer monitor (model ActivPAL4; PAL Technologies Ltd., Glasgow, UK), while using the CREA (v1.3) classification algorithm that allows to distinguish non-wear, lying/sitting, standing, cycling, seated during transport, and stepping time as well as the number of steps and stepping cadence. The ActivPAL combines the information from an inbuilt inclinometer and accelerometer and is the reference objective method for monitoring sedentary activity and transitions from and to this behavior among researchers. Due to its position on the thigh, the ActivPAL permits the distinction between standing (vertical position) from sitting or lying (horizontal position), and the accelerometer data allows to distinguish stationary upright activities (i.e., standing) from upright activities with movement (i.e., stepping). The following variables will be calculated from the device:Mean minutes spent sitting,Mean minutes spent standingMean minutes spent steppingMean number of sit-to-upright transitionsMean minutes spent in prolonged (e.g., bouts of ≥30 min) sittingMean minutes spent sleeping

These variables will be calculated across the total waking day. Participants will wear the device on their right thigh 24 h/day for 7 days at baseline, repeating this assessment at the end of the intervention (after 6 months), and after the follow-up period (after 9 months). The 24 h/day wear period will allow to also collect data on sleep quantity.

More information regarding the procedures related to ActivPAL application are stated in the “Procedures” section.

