## Statistical methods

### Statistical methods for primary and secondary outcomes {20a}

Statistical analysis will be performed using PASW Statistics for Windows version 28.0 (SPSS Inc., an IBM Company, Chicago IL, USA). Data will be analyzed for those having completed pre–post test data and using an intention-to-treat analysis. Baseline differences between the intervention and control group will be examined using independent samples *t*-tests. If exploratory analysis reveals a non-normally distribution for some variables, it will be alternatively used with the non-parametric tests. Repeated measures ANOVA, with time (baseline-M0, M1, and M2) as within-subjects factor and intervention condition as between-subjects factor, will be conducted to evaluate the effects of the intervention on primary and on secondary outcomes. Statistical significance will be set at *p* < 0.05.

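### The voluntary month-3 ActivPAL recording of the primary outcomes has no role in the stated analysis; a baseline-adjusted mixed model could use it without dropping those who decline

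*Protocol article*

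**What the plan says.** The abstract sets the schedule: "Three assessment points will be conducted in both groups, pre-intervention (baseline), post-intervention, and a 3-month follow-up". The section on sedentary and PA pattern assessment has the ActivPAL worn for 7 days at baseline and again at 6 and 9 months, and does not list month 3.

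The primary-outcome text in Outcomes {12} gives the same three moments and then adds a fourth recording: "in the third month of intervention, all participants will be challenged to use the ActivPAL". It continues: "Although this assessment moment is not mandatory, we expect a significant adherence to this challenge". No expected uptake is given as a number.

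Statistical methods {20a} specifies the model: "Repeated measures ANOVA, with time (baseline-M0, M1, and M2) as within-subjects factor and intervention condition as between-subjects factor". The same section says data will be analysed for those with completed pre–post data and by intention to treat. Section {20c} adds that, beyond intention to treat, no statistical technique will be used for missing data.

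The main aim in Objectives {7} is the arm difference after 6 months. A further aim, after the arms swap, includes "the impact of 3 months of sit-stand desks in the control group".

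**The concern.** The trial plans to record its primary outcomes in both arms at month 3, while the arms are still as randomised, and the stated model has no time level for those data. Repeated measures ANOVA needs every level from every participant. Adding a voluntary wave to it would therefore remove everyone who declined, including people with complete baseline and 6-month data.

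Two things are at stake. With only 40 participants, information that could help estimate the 6-month effect when some 6-month recordings are missing is left aside. And because month 3 has no fixed status, a comparison among volunteers could later be reported or left out according to its result. Participants and staff are unblinded after baseline, and only one arm has desks and motivational nudges, so wear at month 3 could differ between arms.

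**Working it through.** The plan gives no month-3 uptake and no correlations, so there is no figure of its own to reproduce. Values marked *assumed* are not in the documents.

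**1. Time points against model levels.** Recordings offered: baseline, month 3 (voluntary), month 6, month 9. Levels in the ANOVA: M0, M1, M2. Month 3 is the one without a level.

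**2. Cost of adding month 3 to the stated ANOVA.** Take 20% missing at month 6 (the protocol's dropout figure) and 80% month-3 uptake (*assumed*, independent of dropout). Complete cases are 0.80 × 0.80 = 0.64, or about 26 of 40, before any month-9 losses. Without month 3 the corresponding figure is 0.80 × 40 = 32.

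**3. Gain from adding month 3 to a mixed model.** *Assumed*: correlation r0 = 0.5–0.6 of each post-baseline recording with baseline, and r = 0.6–0.8 between months 3 and 6, with equal variances. Given baseline, the correlation between months 3 and 6 is p = (r − r0²)/(1 − r0²):

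- r0 = 0.6, r = 0.6: p = 0.24/0.64 = 0.375
- r0 = 0.5, r = 0.8: p = 0.55/0.75 = 0.733

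With independent missingness, 64% have both recordings, 16% month 6 only and 16% month 3 only. In units of the residual variance, the information terms are a = 0.64/(1 − p²) + 0.16 on the diagonal and b = 0.64p/(1 − p²) off it. Relative to a baseline-adjusted analysis of those with a month-6 recording, the variance ratio for the month-6 arm difference is 0.80a/(a² − b²):

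- p = 0.375: a = 0.905, b = 0.279, ratio 0.977
- p = 0.733: a = 1.545, b = 1.015, ratio 0.912

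The variance therefore falls by about 2–9%. This isolates the contribution of month 3; it does not count any benefit of replacing the ANOVA itself. Clustering is ignored. If everyone missing at month 6 also skipped month 3, the month-3-only share would be zero and so would the gain.

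**4. Precision of a month-3 comparison alone.** Two-sample t test, two-sided 0.05, standardised difference 0.80 (the protocol's effect size), clustering ignored:

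| Uptake (*assumed*) | Per arm | Power |
|---|---|---|
| 100% | 20 | 0.69 |
| 80% | 16 | 0.59 |
| 60% | 12 | 0.47 |

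**5. Selection among volunteers, as an illustration.** *Assumed*: uptake of 80% with desks and 60% in controls, and a correlation of 0.2–0.5 between willingness to wear and sitting time. The mean of a standard normal variate above its uptake cut-off is 0.35 at 80% and 0.64 at 60%, a difference of 0.294. The bias is 0.294 × 0.2 = 0.06 SD to 0.294 × 0.5 = 0.15 SD, or 7–18% of 0.80. With equal uptake and the same selection in both arms, this formula gives zero.

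**The case against.** The strongest reply is that nothing here is contradictory. The Outcomes text lists the required moments and then separates the extra one: "2nd moment (i.e., final month of intervention), and 3rd moment (i.e., final month of follow-up). Additionally, in the third month of intervention". An abstract that counts only required moments is condensed, not wrong. **This stands**, and no correction of the three-point count is needed.

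A second reply is that the article does not say month-3 data will be discarded, and that the handling of an optional wave may sit in an analysis plan that is not shown. This stands in part: a reader might infer that the data will be thrown away, and the document does not say so. But the article goes beyond silence. It names the model, fixes its time levels and rules out missing-data methods, and that combination cannot take in a voluntary wave without losing participants.

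Other stronger readings also go too far:

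- *Month 3 is the trial's randomised 3-month desk effect.* No such objective is stated; the 3-month aim concerns former controls after the swap. By month 3 the intervention arm has also had nudges (four in month one, two in each of months two and three) and controls have had none, so the contrast estimates desk plus prompts. Month 9 also compares randomised sequences, although carry-over may affect it.
- *The month-3 data are self-selected.* All participants in both arms are asked and uptake is unknown, so selection is a risk and not a fact.
- *The trial forgoes the equivalent of 15–45% more participants.* That range belongs to the average of months 3 and 6, assuming full uptake. It is a different estimand from the 6-month effect.

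**Conclusion.** The point holds as a modest improvement to the analysis. The stated model gives a planned recording of the primary outcomes no role and is of a kind that could include it only by excluding those who declined. A better method is available at little cost.

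The benefit for the month-6 contrast is about 2–9% lower variance. It rests on the assumed correlations, 20% missing at month 6, 80% uptake, missingness at the two times being independent, and no clustering. It shrinks towards zero if the same people miss both recordings. The 0.06–0.15 SD selection figure is only an illustration, and it would affect only a volunteers-only month-3 comparison, which the article does not propose. The planned 6-month comparison is not biased by leaving month 3 out.

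**What to change.** Analyse the activity outcomes with a likelihood-based mixed model adjusted for baseline, with month 3 as an additional post-baseline time and a separate arm effect at each time. Keep every participant with any post-baseline recording, and keep the month-6 arm difference as the main contrast. Report the month-3 arm difference as a supportive estimate of the desk-plus-prompts package, with the number wearing the device in each arm. Fix this status in writing before the month-3 data are examined.

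If month 3 has not yet passed, present it to both arms as a routine scheduled recording and add it to the ActivPAL schedule. This may be too late: Trial status says the intervention started on 1 March 2023, which puts the third month in May 2023.

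The analysis change costs only wording. Scheduling the recording would cost one more wear week for those who would have declined, plus a protocol amendment, which the article routes through the sponsor and funder, the ethics commission and the registry.

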**Discussion:**

This study will lean on the use of a sit-stand workstation for 6 months, prompted by an initial psychoeducational session and ongoing motivational prompts. We will aim to contribute to this topic by providing robust data on alternating sitting and standing postures in the workplace.

**Trial registration:**

The trial was prospectively registered, and the details are at: https://doi.org/10.17605/OSF.IO/JHGPW; Registered 15 November 2022. OSF Preregistration.

## Administrative information

Note: the numbers in curly brackets in this protocol refer to SPIRIT checklist item numbers. The order of the items has been modified to group similar items (see http://www.equator-network.org/reporting-guidelines/spirit-2013-statement-defining-standard-protocol-items-for-clinical-trials/).

## Introduction

### Background and rationale {6a}

There is a strong interest in capitalizing on years of health and reducing the period of disability in adults to enable well-being in aging. In line with this, it is necessary to further assess the impact of reducing sedentary behavior (SB) or breaking up prolonged bouts of SB on relevant health outcomes, quality of life, and productivity throughout the lifespan [1].

The evidence supporting the importance of reducing SB is plentiful; high levels of SB are linked with physical inactivity (i.e., not attaining the recommended amount of physical activity (PA), which in turn has been associated with obesity [2], metabolic disorders [3, 4], and all-cause mortality [5, 6]. In addition to physical inactivity, the negative role of excessive SB on health has been identified, with SB being linked to all-cause and cardiovascular diseases (CVD) mortality [7, 8] and to decreased life expectancy, with 3 h of sitting per day leading to a life expectancy decrease of 2 years [9, 10]. Martinez-Gomez and colleagues showed that older adults who spent less than 8 h sitting/day had a lower risk of all-cause mortality, when compared with their sedentary peers [11]. A prospective study found that during 6.8 years, greater sitting time (≥12 vs <5 h/day) was associated with increased risk for all-cause and CVD mortality [7], and that in less-active adults, replacing 1 h/day of sitting with an equal amount of activity was associated with lower all-cause mortality for both exercise and non-exercise activities. Recently, it was found that replacing SB with light-intensity physical activity (LIPA) may protect against cognitive decline by reducing glycemic variability [8] and increasing cerebral blood flow [12].

In addition, SB and PA seem to be independently related to functional fitness in older adults [13]. Interestingly, breaking up SB seems to be even more important than total SB; it has been associated with lower abdominal obesity in older women [14] and each transition between sitting and standing (i.e., break in sedentary time) entails high energy expenditure [15], suggesting that prolonged SB must be avoided [16]. Breaking up SB is also positively associated with physical function [17] and the capacity to perform activities of daily living in older adults [18]. Moreover, in patients with type two diabetes, breaking SB more often was associated with higher levels of brain-derived neurotrophic factor (BDNF), a cognitive and memory indicator, which is additionally responsible for fat oxidation in the muscle [19].

SB has also been linked to food consumption across the lifespan, particularly to spontaneous compensations in habitual nutrition (with greater consumption of energy-dense snacks and sugar sweetened beverages and fewer fruits and vegetables) [20]. Although evidence is still in its early stages, a recent study by Grant and colleagues indicates that displacing SB with LIPA improves dietary quality in older females and that SB fragmentation appears advantageous for various dietary outcomes [21]. These findings suggest that replacing SB with a variety of activities is important, regardless of their intensity; however, the next step is to confirm these hypotheses in experimental studies.

The World Health Organization (WHO) data indicates that workers represent approximately half the global population and that most of the population spends an average of one-third of their adult life at work—in jobs that augment SB by sitting and commuting. As such, employers have an opportunity to create supportive environments to encourage workers to reduce SB. Consequently, researchers should prioritize the study of the effectiveness of reducing SB’ interventions at the organizational level [22, 23]. Indeed, office-based workers are highly sedentary due to the job demands (e.g., meetings, working with a computer), making them a key target group for intervention [24].

In office-based workers, higher SB has been associated with lower job satisfaction and greater fatigue, when compared with lower SB. Results offer promising support that less sitting time is associated with positive outcomes that do not seem to come at the expense of productivity [25]. Thus, the office is a key setting to reducing prolonged SB [26, 27], and this is an important consideration in the context of the duty of care obligations of employers to ensure, so far as it is reasonably feasible.

Several sit-stand desk-based RCT interventions have been performed worldwide. In the last decade, most of them took place in Oceania, with 4 being held in Australia [28–31] and 3 in New Zealand [32–34]. Five interventions were held in the United Kingdom (UK) [35–39] and 2 interventions in Canada [40, 41]. The United States of America (USA) contributed with 5 sit-stand desk-based RCTs [12, 42–45] and Japan with 1 intervention [46]. Notice that 14 out of the 23 RCTs were performed in countries belonging to the Commonwealth, and 19 out of 23 in English-speaking countries. In Europe, there is a lack of interventions using sit-stand desks, with only 1 in Finland [47], 1 in Austria [48], and 1 in Switzerland [49]. There is a need for more evidence on the implementation acceptance and effectiveness of these new approaches in the work environment, especially in non-English-speaking countries. While several interventions seemed effective at reducing SB in the workplace [31, 50–58], there is no information from Portuguese-speaking countries, when considering the adult population, which deserves our attention.

### Objectives {7}

This paper describes the protocol for a cluster randomized controlled trial (RCT) the Standing Up for Healthy Aging (SUFHA), which aims to evaluate the change in sedentary patterns (i.e., quantity and accumulation pattern) resulting from the introduction of a health-enhancing contextual modification (i.e., sit-stand desk) in the workplace, compared to a control group after 6 months of intervention (i.e., effectiveness). Secondary outcomes are body composition, eating patterns, health and work-related outcomes, skeletal muscle discomfort, well-being, and quality of life. Additionally, we aim to crossover the intervention and test the impact of 3 months without the sit-stand desks on sedentary patterns in the intervention group and the impact of 3 months of sit-stand desks in the control group, and the level of acceptance regarding the use of these sit-stand desks in both groups.

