There is evidence that temporary context changes, such as holidays, threaten to derail newfound routines, such as standing more often in the workplace [39]. Furthermore, after the intervention period, participants will no longer have the sit-stand desk. Thus, to enhance motivation and self-regulation for internalizing the new routines of breaking up sitting time, intervention participants will also be provided motivational nudges throughout the intervention. Delivery of these nudges will vary from 4 times in the first month, to 2 times in the second and third months, and monthly until the end of the intervention. These motivational nudges will be delivered in different formats, designed to be appealing and engaging (e.g., animated short videos containing simple tips on different forms of breaking sitting time and benefits of that); social support and social modeling will also be enhanced via these nudges (e.g., including testimonials from study participants willing to share their ongoing experience, including photos and short videos using the desk) allowing to support relatedness, perceived competence, and autonomy to use the desk. These are the three basic psychological needs supporting autonomous motivation according to Self-Determination Theory [60]. This type of motivation, in turn, has been shown to allow the integration of new health behaviors in the long term while also enhancing well-being [61].

To determine if the outcomes’ changes observed during the 6 months of work can be maintained in a context without the stimulus (i.e., no sit-stand desk), the intervention group will be followed for 3 months, in which they will be without the sit-stand desks. By the end of the intervention period and at the end of the follow-up, assessments will be conducted, and feedback provided to all participants assuring valuable information regarding participants sedentary patterns, body composition, eating patterns, health and work-related outcomes, fatigue, presenteeism, job satisfaction, well-being, and quality of life, and information on how these have changed over the course of the study.

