### Participant timeline {13}

The time schedule of enrolment, interventions, assessments, and visits for participants are presented in a diagram (see Fig. 1). All participants will enter the study and be assessed at the same time points.

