Besides the introduction of a contextual change in the workplace (i.e., sit-stand desk), this intervention will use an initial psychoeducational session to all participants, to inform about the harms of spending too much time sitting and the independent health benefits of interrupting this behavior more often. Furthermore, a motivational system of prompts will also be offered, nudging participants to stand more often, for 6 months. After the initial 6 months of the intervention, the control group will receive the sit-stand desk, and the intervention group will be without the stimulus, to observe if the new habits gained during the intervention period somehow remain after 3 months of follow-up (i.e., without the sit-stand desks). A major strength of the SUFHA is that it builds on previous interventions using sit-stand desks around the globe to target office workers in a university setting. Previous interventions have been combining sit-stand desk in addition to other strategies (i.e., multicomponent interventions) such as the usage of pedometer and/or competition among participants, or other strategies [79, 80], which makes it difficult to isolate the impact of simply using these sit-stand desks; SUFHA intends to fill this gap and extending it by providing data on maintenance of the new habits. Furthermore, feedback on the barriers and facilitators of the use of the sit-stand desks will also be collected via focus groups exploring the experiences of the participants during the trial.

The findings from this cluster RCT will provide insight for future research studies, as well as real-world interventions, and offer evidence for policy guidelines around workplace health and well-being.

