## Trial status

The current protocol version is dated 11/2/2023. The recruitment began on the 1st of January 2023 and ended by the end of February 2023. On the 1st of March, the intervention kicked off and is currently ongoing. Two more moments of assessment will still occur. Due to some delay in the revision of the final draft of the manuscript, we were not able to submit the manuscript prior to the last participant being recruited.

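### The swap-phase aim asks for separate effects of desk removal and desk introduction, but both arms switch together, so neither one-arm change from M1 to M2 can be told apart from a common time shift

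*Protocol article*

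**What the plan says.** Objectives {7} gives the main 6-month aim a comparator, the control group. The additional aim for the swap phase has none. It is to "test the impact of 3 months without the sit-stand desks on sedentary patterns in the intervention group and the impact of 3 months" with desks in the control group. Intervention description {11a} repeats the removal question for one arm only: to see whether changes are maintained, "the intervention group will be followed for 3 months, in which they will be without the sit-stand desks". The Discussion returns to the same question and confirms that both arms change condition together: "the control group will receive the sit-stand desk, and the intervention group will be without the stimulus".

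The timing is common to everyone. Participant timeline {13} states: "All participants will enter the study and be assessed at the same time points". The primary outcomes section sets the assessments at baseline, "2nd moment (i.e., final month of intervention), and 3rd moment (i.e., final month of follow-up". Trial status gives the start: "On the 1st of March, the intervention kicked off and is currently ongoing".

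The only model named, in Statistical methods {20a}, is "Repeated measures ANOVA, with time (baseline-M0, M1, and M2) as within-subjects factor and intervention condition as between-subjects factor". That section links no term or contrast of the model to the swap-phase aim.

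**The concern.** An effect of removal in one arm and an effect of introduction in the other are most naturally read off each arm's change from M1 to M2. The null hypothesis of such a comparison is that mean sitting time does not change over those three months. That equals no desk effect only if nothing else changes over the same period.

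The protocol itself gives reasons to doubt this. Intervention description {11a} says that "temporary context changes, such as holidays, threaten to derail newfound routines", and M1 falls at about August. Feedback on personal results is planned for all participants around M1, and the retention section {18b} withholds baseline feedback from controls because it could alter their behavior. The outcomes cover the whole waking day, so changes outside work count too.

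At stake is the reading of the follow-up results, which Dissemination plans {31a} assigns to a paper of their own. A common fall in sitting could make habits appear to have persisted after removal and make introduction look stronger than it is. A common rise would do the reverse.

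**Working it through.** **1. What each contrast estimates.** Let R be the rise in sitting caused by removing the desk, I the fall caused by introducing it, and g a shift from M1 to M2 common to both arms (positive means more sitting).

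- Intervention arm, M2 minus M1: R + g
- Control arm, M2 minus M1: -I + g
- Between-arm difference in change: (R + g) - (-I + g) = R + I

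The one-arm changes always contain g. The between-arm contrast does not, but it gives only the sum R + I. There are two observed changes and three unknowns, so R and I are not separately identified.

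**2. Calendar.** With a start on 1 March, the final month of a 6-month intervention is about August, and the final month of the following 3 months is about November, for all participants.

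**3. What the planned model offers.** In the three-level time-by-condition ANOVA:

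- the time main effect averages the two arms, so it answers neither one-arm question;
- the omnibus interaction tests whether the between-arm difference is constant over M0, M1 and M2. If that difference is 0 at M0 and -D at both M1 and M2, the interaction is non-zero although nothing happened at the swap (R + I = 0). It can therefore be significant from M0-M1 alone;
- the M1-M2 component of the interaction is the R + I contrast of step 1.

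**4. Size if one-arm tests were used.** The plan gives no figure for this to reproduce. Inputs:

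- n = 17 and 20 per arm, from the 34 and 40 participants in Sample size {14}, divided by 2;
- two-sided 5%, from the same section;
- M1-M2 correlation r = 0.5 to 0.7 and shift g in SD units: **assumed**, since the documents give neither.

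The SD of the change is sqrt(2(1 - r)), which is 1.000 at r = 0.5 and 0.775 at r = 0.7. The noncentrality of the paired t test is g × sqrt(n) / sqrt(2(1 - r)). For example, g = 0.3, n = 17 and r = 0.5 give 0.3 × 4.123 / 1.000 = 1.24, and a rejection probability of 0.214.

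Rejection probability of a one-arm M1-M2 test with no desk effect (R = I = 0):

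| Common shift g | r = 0.5, n = 17 | r = 0.5, n = 20 | r = 0.7, n = 17 | r = 0.7, n = 20 |
|---|---|---|---|---|
| 0 | 0.050 | 0.050 | 0.050 | 0.050 |
| 0.1 SD | 0.067 | 0.071 | 0.079 | 0.085 |
| 0.2 SD | 0.121 | 0.136 | 0.170 | 0.195 |
| 0.3 SD | 0.214 | 0.247 | 0.324 | 0.376 |
| 0.5 SD | 0.491 | 0.565 | 0.705 | 0.782 |

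A simulation at r = 0.5 (20,000 runs per setting, independent participants) agrees with these figures. In it the between-arm contrast rejects 4.8-5.2% of the time for every shift tried, from 0 to 0.8 SD.

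**5. Opposite distortion in the two arms.** Take R = I = 0.4 SD, g = -0.3 SD and r = 0.5, all assumed.

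- Removal arm: 0.4 - 0.3 = 0.1 SD, power 7%
- Introduction arm: -0.4 - 0.3 = -0.7 SD, power 77% (n = 17) to 84% (n = 20)
- Between-arm contrast: 0.4 + 0.4 = 0.8 SD, power 62% to 69%, whatever g is

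Equal true effects would look sharply unequal for calendar reasons alone.

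**The case against.** The strongest reply is that the protocol specifies no within-arm test. Its one named model has condition as a between-subjects factor, and its time-by-condition interaction contains the contrast that is wanted. The sentence in Objectives {7} can be read as saying which arm receives which condition after the switch, not how an effect will be estimated. The choice of follow-up contrasts is often left to a statistical analysis plan, and none is shown here. The sizes of the shift and of the correlation are assumed. Finally, the sum R + I does not answer the maintenance question, so making it the test changes the question.

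Much of this stands. A reader might infer that the plan tests each arm's change and would declare any common trend a desk effect. The documents do not support that: no such test is named, a 0.1 SD shift would raise rejection only to 7-9%, and a shift masks or reverses one arm's apparent effect while it inflates the other's. The limit on the sum is also real and has to be stated.

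The reply does not remove the point about the aim itself. Objectives {7}, Intervention description {11a} and the Discussion ask for effects that this design cannot separate from calendar time, whichever contrast an analysis plan selects. The omnibus interaction of the named model does not isolate the swap either.

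**Conclusion.** The point holds as a mismatch between a stated aim and what the design can identify. Removal and introduction are asked for as separate effects, but both arms switch together and neither serves as an unchanged concurrent control.

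The error rates in the working are conditional: they apply only if the aims are answered by one-arm M1-M2 tests, they rest on an assumed shift and correlation, and they ignore clustering. The documents establish that a common shift is plausible, not how large it is. The between-arm contrast is protected only against a shift that is the same in both arms.

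The change should be made, but its reach is limited. This is an additional aim, and the main 6-month between-arm comparison is not affected.

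**What to change.** - In Statistical methods {20a}, pre-specify the between-arm difference in change from M1 to M2 (the M1-M2 component of time by condition) as the inferential test for the swap phase, in place of the three-level omnibus interaction.
- State that it estimates the combined effect of removing and introducing the desk, and that it does not by itself answer whether habits were maintained.
- Report each arm's M1-M2 change descriptively with a confidence interval, noting that it includes any common time shift.
- Reword Objectives {7}, and the matching sentences in Intervention description {11a} and the Discussion, so that neither one-arm change is claimed as the effect of removal or introduction alone.

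The cost is a change of wording and one contrast on assessments already planned, with no new data. The downside is that removal and introduction cannot be separated without assuming no common trend, so the maintenance question gets a descriptive answer only.
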